#### **Resumption of treatment following allergic/hypersensitivity reactions:**

Once the cetuximab infusion rate has been decreased due to an allergic/hypersensitivity reaction, it must remain decreased for all subsequent infusions. If the subject has a second allergic/hypersensitivity reaction on the slower infusion rate, the infusion should be stopped and the subject should not receive any further cetuximab treatment. If a subject experiences a Grade 3 or 4 allergic/hypersensitivity reaction at any time, cetuximab must be discontinued.

#### 10.3.2.2. Skin Toxicity

If a subject experiences Grade 3 skin toxicity, cetuximab therapy may be delayed for up to 14 days without changing the dose level (see [Figure 3](#)). The investigator should also consider concomitant treatment with topical and oral antibiotics; topical corticosteroids are not

recommended. If the toxicity resolves to Grade 2 or less by the following treatment period, treatment may be resumed. If Grade 3 skin toxicity occurs for a second and third time, cetuximab therapy may again be delayed for up to 14 days with concomitant dose reductions to 200 mg/m^2 and then 150 mg/m^2. Cetuximab dose reductions are permanent. Subjects must discontinue cetuximab if more than 2 consecutive infusions are withheld or Grade 3 skin toxicity occurs for a fourth time despite appropriate dose reduction.

**Figure 3: Treatment Adjustments for Cetuximab-Related Skin Toxicity**

[figure not shown]

#### 10.3.2.3. Additional Cetuximab Considerations

In addition to omissions and discontinuation for the above reasons, cetuximab may have to be delayed or discontinued if a subject develops an intercurrent illness (e.g. an infection). If in the opinion of the investigator, this warrants interruption of cetuximab therapy, the intercurrent illness must resolve within a time frame such that no more than 2 consecutive infusions are withheld. After the interruption of treatment, the patient will continue with cetuximab at the assigned dose level. The higher initial dose is not repeated.

If therapy must be withheld for > 14 days, the study treatment will be discontinued.

### 10.4. Prior/Concomitant Medications

All medications (prescription and non-prescription), treatments and therapies taken at the time of study start through 28 days after the last dose of investigational product(s), must be recorded on the appropriate page of the CRF.

#### 10.4.1. Permitted Concomitant Therapy

- Pre-medication for investigational products.

- Full supportive care is permitted when appropriate, including transfusions of blood and blood products, antibiotics, or antiemetics.
- The use of growth factors is permitted according to ASCO guidelines.
- Histamine-receptor antagonists or proton-pump inhibitor therapy is permitted.
- Anticoagulants are permitted.
- Narcotic and non-narcotic analgesics are permitted.

#### **10.4.2. Prohibited Concomitant Therapy**

- Treatment with anti-cancer agents is not permitted (except investigational products as per protocol).
- Radiation therapy is not permitted.
- Use of any other experimental drug or therapy is not permitted.

### **10.5. Treatment Compliance**

Study personnel will be instructed to complete pill counts of unused medication at Day 1 of each cycle and at study discontinuation (see appropriate handling instructions in the Pharmacy Manual). Compliance is defined as taking  $\geq 70\%$  of the assigned study medication dose during any cycle for reasons other than toxicity or treatment hold in accordance with the protocol. Lack of compliance may lead to discontinuation from the study at the discretion of the Investigator and/or sponsor. Any investigational product (lenalidomide and/or cetuximab) held  $> 14$  days must be discontinued.

### **10.6. Discontinuation from Treatment**

The following events are considered sufficient reasons for discontinuing a subject from investigational product(s):

- Adverse event(s) (AEs) that, in the judgment of the Investigator, may cause severe or permanent harm or which rule out continuation of investigational product(s).
- Disease progression
- Subject withdraws consent
- Subject lost to follow-up
- Death
- Protocol violation

The reason for discontinuation should be recorded in the CRF and in the subject's medical records. An IVRS call is required when discontinuing any investigational product.

## **11. INVESTIGATIONAL PRODUCT MATERIALS AND MANAGEMENT**

### **11.1. Supplier(s)**

Celgene Corporation will supply lenalidomide and commercial cetuximab labeled as IMP.

### **11.2. Dosage Form**

Celgene Corporation will supply lenalidomide as 5, 10, 15, 20, and 25 mg capsules for oral administration.

Celgene Corporation will supply commercial cetuximab labeled as IMP for IV infusion.

### **11.3. Dosage Regimen**

Lenalidomide will be administered PO once daily on Days 1-28 of each 28-day treatment cycle. Lenalidomide should be taken at approximately the same time each day.

Cetuximab will be administered via IV infusion on Days 1, 8, 15 and 22 of each 28-day cycle. The initial dose of cetuximab will be administered at 400 mg/m^2, then 250 mg/m^2 weekly thereafter.

### **11.4. Investigational Product Packaging and Labeling**

Celgene Corporation will supply lenalidomide investigational product packaged in open-label bottles containing enough supply for a 28-day cycle. Each subject will take one capsule per day orally.

Celgene Corporation will supply commercial cetuximab labeled as IMP.

The investigational product(s) label will bear Celgene's name, address, and telephone number, the protocol number, EudraCT number (where required), product name, dosage form and strength, quantity of investigational product per container, lot number, expiration date, medication identification/kit number, dosing instructions, storage conditions, and required caution statements and/or regulatory statements as applicable. Additional information may be included on the label as applicable per local regulations.

Subjects requiring dose reduction within a treatment cycle must return to the study site and return the empty bottle or any unused product and a new bottle will be dispensed.

### **11.5. Investigational Product Receipt and Storage**

The Investigator(s) is responsible for taking an inventory of each shipment of investigational product(s) received, and comparing it with the accompanying investigational product(s) shipping order form. The Investigator(s) will verify the accuracy of the information on the form and call the IVRS to register the study medication received at the site.

At the study site, all investigational product(s) will be stored in a locked, safe area to prevent unauthorized access.

The investigational product should be stored as directed on the product label.

#### **11.6. Record of Administration**

Accurate recording of all investigational product(s) administration (including dispensing and dosing) will be kept.

#### **11.7. Investigational Product Accountability**

The investigator(s) or designee(s) is responsible for accounting for all investigational product(s) issued to, and returned by, the subject during the course of the study.

#### **11.8. Investigational Product Handling and Disposal**

Celgene will instruct the Investigator(s) on drug handling and the return or destruction of unused investigational product(s) per local standard practice. If any investigational product(s) is lost or damaged, its disposition should be documented. Celgene Corporation will provide instructions for the return of investigational product at the end of the study.

## **12. ASSESSMENT OF EFFICACY**

### **12.1. Assessments**

- Tumor assessment.
- Response assessment (RECIST 1.1).
- ECOG performance status.
- Overall survival.

### **12.2. Methods and Timing of Efficacy Assessments**

The efficacy assessments will be conducted at timed intervals during the study as specified in [Table 2](#).

#### **12.2.1. Tumor Assessment**

Tumor assessment conventional (or spiral) CT, or MRI will be performed at screening, every 2 cycles beginning with Cycle 3 Day 1, and at treatment discontinuation. Subjects who have received screening scans within 28 days of Cycle 1 Day 1 do not need to have an additional scan done. Discontinuation from study scans do not need to be done if last scan was performed within the prior 28 days. During the study, scans must be done up to 7 days prior to Day 1 of the cycle. To ensure comparability, baseline methods and on-study methods for tumor assessment must be performed using identical techniques. X-rays will be performed only when clinically indicated.

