### **Efficacy Assessments**

-  Conventional (or spiral) CT/MRI scans are required. Subjects having received a scan during the Screening Period are not required to have a scan at Cycle 1 Day 1.
-  Conventional (or spiral) CT/MRI scans are required every 2 cycles beginning with Cycle 3 Day 1. Scans must be done within 7 days prior to Day 1 of the cycle. To ensure comparability, baseline methods and on-study methods for tumor assessment must be performed using identical techniques. Chest X-ray may be performed only when clinically indicated.
-  Scan should be performed at treatment discontinuation unless last scan was performed within the prior 28 days.
-  Tumor response will be evaluated every 2 cycles beginning with Cycle 3 Day 1 and at treatment discontinuation. Response and progression will be evaluated using the RECIST 1.1

criteria. All subjects with evidence of objective tumor response (CR and PR) should have the response confirmed at the next scheduled scan (every 2 cycles following Cycle 1 Day 1).

-  Survival data will be captured via phone contact every 90 days until death or 5 years post-discontinuation.

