#### 8.1.1. Safety Lead-In Dose Finding

Initially 6 subjects will be enrolled and treated with a daily oral dose of lenalidomide at 25 mg administered on Days 1-28 of each 28-day cycle and intravenous (IV) infusions of cetuximab (400 mg/m^2 first infusion only, then 250 mg/m^2 subsequently) administered on Days 1, 8, 15, and 22 of each 28-day cycle.

- If < 2 of the 6 subjects experience a Dose Limiting Toxicity (DLT), then the Phase 2b – POC part will start with lenalidomide at 25 mg.
- If  $\geq 2$  of the 6 subjects experience a DLT, then 6 additional subjects will be enrolled at lenalidomide 20 mg.
  - If < 2 of the additional 6 subjects experience a DLT, then the Phase 2b – POC part will start with lenalidomide at 20 mg.
  - If  $\geq 2$  of the additional 6 subjects experience a DLT, then 6 additional subjects will be enrolled at lenalidomide 15 mg.
    - If < 2 of the additional 6 subjects experience a DLT, then the Phase 2b – POC part will start with lenalidomide at 15 mg
    - If  $\geq 2$  of the additional 6 subjects experience a DLT, then Celgene Corporation will discuss with the investigators and reassess the doses.

Dosing does not escalate during the safety lead-in part of the study. In addition, there will be no intra-patient dose escalation. Cycles will be repeated every 28 days. All subjects will continue on

investigational product(s) until documented tumor progression, unacceptable toxicity, death, or treatment discontinuation for any other reason.

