### **8.1.2. Safety Lead-In Definition of Dose Limiting Toxicity**

DLT is defined as one or more of the following:

- Total of  $\geq 7$  days of lenalidomide and/or  $\geq 1$  dose of cetuximab missed during the first cycle due to drug-related toxicity as outlined below:
  - Any Grade 3 or 4 non-hematological toxicity (excluding alopecia), even after optimally treated with supportive measures.
    - A rash with suspected relationship to cetuximab, treated and resolved in accordance with the guidelines will not be considered a DLT.
  - Grade 4 neutropenia or febrile neutropenia.
  - Grade 4 thrombocytopenia.

Should any subject discontinue the study prior to completing the entire first cycle for reasons other than a DLT or if  $\geq 7$  days of lenalidomide and/or  $\geq 1$  dose of cetuximab were missed during the first cycle for reasons other than a DLT, then a replacement subject will be added at that dose level.

The occurrence of one of the above drug-related toxicities will result in a clinical and/or laboratory assessment to be performed within 7 days following the initial finding to examine the subject for resolution of the toxicity. Lack of resolution of any of these toxicities according to the guidelines above or within 7 days of scheduled start of Cycle 2 Day 1 will be considered a DLT. Subjects who experience a DLT may continue on treatment at the Investigator's discretion at a lower dose of lenalidomide in accordance with [Table 6](#).

Adverse events will be graded using the CTCAE Version 4.0 ([http://ctep.cancer.gov/protocolDevelopment/electronic\\_applications/docs/ctcae4.pdf](http://ctep.cancer.gov/protocolDevelopment/electronic_applications/docs/ctcae4.pdf)).

If cetuximab is discontinued, lenalidomide may be continued until documented tumor progression, unacceptable toxicity, death, or treatment discontinuation for any other reason.

Following Cycle 1, all subjects will continue on assigned treatment until documented tumor progression, unacceptable toxicity, death, or treatment discontinuation for any other reason and be followed for toxicity and secondary endpoints.

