### **10.3. Dose Modification or Interruption**

Dose modifications of lenalidomide and cetuximab are not permitted during Cycle 1 of the Phase 2a – Safety Lead-In part, unless a subject experiences a DLT, however permitted anytime after Cycle 1 during Phase 2a – Safety Lead-In, anytime during Phase 2b –POC and Phase 2b – Expansion.

For toxicities consistent with cetuximab administration, discontinuation, dose interruptions and/or reductions see Section 10.3.2 and the approved product labeling. If toxicities are believed to be attributed to lenalidomide administration, please see Table 6 for dose modification guidelines. Doses of any investigational product cannot be re-escalated once reduced. Any investigational product (lenalidomide and/or cetuximab) held > 14 days must be discontinued. If cetuximab is discontinued per protocol and for reasons other than disease progression, lenalidomide may be continued until documented tumor progression, unacceptable toxicity, death, or treatment discontinuation for any other reason.

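### Scan dates follow cycle Day 1 with no calendar anchor, so if a dose hold postpones Day 1, recorded PFS and duration of response can shift (minor)

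*Protocol*

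**What the plan says.** Section 12.2.1 of the protocol sets on-treatment scans "every 2 cycles beginning with Cycle 3 Day 1, and at treatment discontinuation" and adds that "scans must be done up to 7 days prior to Day 1 of the cycle". Table 2 footnote 11 repeats the window: "Scans must be done within 7 days prior to Day 1 of the cycle". Section 12.2.2 and footnote 13 put response assessment on the same two-cycle schedule, with confirmation at the next scheduled scan.

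On cycle timing, section 8.1.1 says "Cycles will be repeated every 28 days". On interruptions, section 10.3 says "Any investigational product (lenalidomide and/or cetuximab) held > 14 days must be discontinued". Section 10.3.2.2 says that after Grade 3 skin toxicity "cetuximab therapy may be delayed for up to 14 days without changing the dose level". If cetuximab is stopped for reasons other than progression, "lenalidomide may be continued until documented tumor progression, unacceptable toxicity, death, or treatment discontinuation for any other reason" (section 10.3). The only text that hints at a planned cycle start differing from the actual one is the dose-limiting toxicity definition in section 8.1.2, which judges resolution "within 7 days of scheduled start of Cycle 2 Day 1". That definition applies to the Phase 2a lead-in only.

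PFS and duration of response are secondary endpoints (section 7.2). Section 15.2 plans Kaplan-Meier estimates for them if there are enough data.

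**The concern.** Progression without death is recorded at a scan. If the scan date depends on dosing, anything that delays dosing also delays the date on which progression can be recorded, and measured PFS lengthens without any antitumor effect. The same holds for the first-response date and for progression after response, so duration of response runs on the same clock.

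The window reinforces this. Because it is one-sided and mandatory, a site that postpones Day 1 cannot keep the scan on its planned date and stay within protocol. The protocol also leaves open whether a hold postpones Day 1, so two sites could read it differently and scan comparable subjects on different dates. At stake are the PFS and duration-of-response estimates for the two randomised POC arms and for the Expansion part. Scan timing lost during conduct cannot be recovered in the analysis.

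**Working it through.** **1. Figures the protocol does state.** Section 15.7 gives no PFS assumption, event count or power. Its response-rate figures reproduce:
- POC design: the probability of a positive arm is the sum over x1 = 3 to 23 of P(X1 = x1) × P(X2 ≥ 9 − x1), with X1 ~ Bin(23, p) and X2 ~ Bin(18, p). At p = 0.10 this is 0.0178 (limit 0.025). At p = 0.30 it is 0.902 (stated 90%).
- Expansion: the exact 95% interval for 36/120 is 22.0% to 39.0%, as stated.

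These rules count responders and use no progression date, so scan timing does not enter them.

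**2. What the window does if Day 1 moves.** Counting Cycle 1 Day 1 as day 1, Cycle 3 Day 1 falls on day 1 + 2 × 28 = 57, and the scan window is days 50 to 57. If Day 1 slips 14 days it falls on day 71 and the window becomes days 64 to 71. A scan on the original day 57 would then be outside the window.

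**3. Size of the shift in the mean.** The protocol gives no PFS median and no delay rate, so these are assumptions: exponential progression with true median m of 42, 56, 84 or 112 days; nominal scan spacing 2 × 28 = 56 days; each two-cycle interval lengthened by d days with probability p; progression recorded at the next scan; no deaths or censoring.

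Mean recorded PFS = E[S] / (1 − E[2^(−S/m)]), where the interval S is 56 with probability 1 − p and 56 + d with probability p.

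Worked case, m = 56, d = 14, p = 0.5:
- E[S] = 63
- E[2^(−S/m)] = 0.5 × 0.5000 + 0.5 × 0.4204 = 0.4602
- mean = 63 / 0.5398 = 116.7 days, against 56 / 0.5 = 112.0 with no slips, a rise of 4.7 days

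| Slip | m = 42 | m = 56 | m = 84 | m = 112 |
|---|---|---|---|---|
| None (mean, days) | 92.8 | 112.0 | 151.3 | 191.2 |
| 7 days in 25% | +1.2 | +1.2 | +1.1 | +1.1 |
| 7 days in 50% | +2.4 | +2.3 | +2.1 | +2.1 |
| 14 days in 25% | +2.6 | +2.5 | +2.3 | +2.3 |
| 14 days in 50% | +5.0 | +4.7 | +4.5 | +4.3 |
| 14 days in all | +9.3 | +8.8 | +8.2 | +7.9 |

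Simulation with the same inputs agrees with these values to within a fraction of a day.

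**4. The median.** It can fall only on a scan date, so it moves in jumps.
- True median 84 days: 37.0% have progressed by day 56 and 60.3% by day 112, so the recorded median is 112. With a 14-day slip in every interval the scans fall on days 70 and 140, with 43.9% and 68.5% progressed, and the recorded median is 140. With slips in 25% of intervals it stays at 112.
- True median 42 days: 60.3% have progressed by day 56. If a share q of subjects have a 14-day slip before the first scan, 0.603 × (1 − q) are recorded by day 56. This is below one half once q exceeds 1 − 0.5/0.603 = 0.17, and the recorded median then moves from 56 to 70 days.

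True medians of 56 and 112 days put exactly half the progressions on a scan date. The recorded median is then unstable and is not used here.

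**The case against.** The strongest reply is that the premise is not in the protocol. Cycles repeat every 28 days, Table 6 holds a drug and not a cycle, and sections 8.1.2, 10.3.2.2 and 10.3.2.3 count missed days or withheld infusions. A dose missed inside a running cycle leaves the scan where it was. Read that way, every two cycles already means every 56 days. This reading is tenable, and the effect is zero under it. What survives is that the protocol does not say so, and the scheduled-start wording in section 8.1.2, even though confined to Phase 2a, points the other way.

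A reader might infer that the schedule must favour the combination arm because it carries two drugs' worth of interruption rules. The documents do not support that. The hypersensitivity rules in section 10.3.2.1 slow, pause or end cetuximab and contain no delay between doses. The skin-toxicity rule delays cetuximab only and does not stop daily lenalidomide. Arm 1 may receive a lower lenalidomide dose than Arm 2, depending on the lead-in. No toxicity or delay rates by arm are given.

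A reader might also infer that a planned comparison is biased. None is planned: each POC arm is judged alone on response rate, the primary efficacy analysis uses the Expansion part alone (section 15.6), and section 15.2 offers PFS estimates without a test. Section 15.3 does call for analyses by treatment group, so the two randomised arms' curves are still likely to be read side by side.

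Finally, the 14-day limit and the scan at treatment discontinuation restrain the shift. The restraint is partial. The limit is worded for a hold, with no cumulative cap stated, and two cycle starts precede the first scan. The discontinuation scan is waived if one was done in the prior 28 days and does nothing for a subject who stays on treatment. A 28-day slip in 25% of intervals would add about 5 to 6 days to the mean in the same simulation.

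**Conclusion.** The point holds in a limited form. Scans and response assessments are tied to cycle Day 1 without a calendar anchor, and the protocol is silent on whether a hold moves Day 1. If it does, recorded PFS and duration of response can shift, by more in whichever arm has more cycle delays; that arm cannot be identified from the documents. Against a 56-day scan interval, the shift in mean PFS is about 1 to 5 days under partial delay and 8 to 9 days if every interval slips 14 days. The median can move by 14 to 28 days because it can fall only on scan dates. These sizes rest on assumed medians, assumed delay frequencies and exponential progression. If Day 1 never moves, the shift is zero. The primary response-rate rules do not depend on it. Severity is minor: a cheap improvement for descriptive secondary endpoints.

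**What to change.** In sections 12.2.1 and 12.2.2 and Table 2 footnotes 11 and 13, state that scans and response assessments occur every 8 weeks (56 days) counted from Cycle 1 Day 1, with a fixed window (for example ± 7 days), regardless of dose holds or cycle delays. Put confirmation of response on the same calendar schedule. This removes the delay-related shift whichever way a hold affects Day 1, so it requires no change to the dosing rules.

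The cost is protocol wording and the same number of scans, or nearly so. The small downside is that after a delay a scan may fall away from a dosing visit.

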#### **12.2.2. Response Assessment**

Tumor response will be evaluated every 2 cycles beginning with Cycle 3 Day 1 and at treatment discontinuation. Response and progression will be evaluated using the RECIST 1.1 criteria ([Eisenhauer, 2009](#)). All subjects with evidence of objective tumor response (CR and PR) should have the response confirmed with repeat assessments performed at the next scheduled scan (every 2 cycles following Day 1 Cycle 1).

#### **12.2.3. ECOG Performance Status**

ECOG Performance Status will be evaluated during screening, every cycle Day 1 (pre-dose), and at treatment discontinuation.

#### **12.2.4. Survival**

All subjects will be followed for survival every 90 days after discontinuation via phone contact until death or 5 years post discontinuation.

